**Methods:**

This is a multicenter phase II rater-blinded randomized controlled trial in which 80 FEP patients with a history of psychological trauma will be randomly assigned to EMDR (n = 40) or to TAU (n = 40). Traumatic events will be measured by the Global Assessment of Posttraumatic Stress Questionnaire, the Cumulative Trauma Screening, the Impact of Event Scale-Revised, the Dissociative Experiences Scale, the Childhood Trauma Scale, the Holmes–Rahe Life Stress Inventory, and the Dissociative Experiences Questionnaire. Clinical symptomatology will be evaluated using the Suicide and Drug Consumption module of the International Neuropsychiatric Interview, Structured Clinical Interview for Positive and Negative Syndrome Scale, Young’s Scale for Mania Evaluation, and Beck Depression II Questionnaire. Functionality will be assessed with the Global Assessment of Functioning and the Quality of Life with the Standardized Instrument developed by the EuroQol Group. The cognitive insight and adherence to the treatment will be assessed with the Beck Cognitive Insight Scale and the Drug Attitude Inventory. All variables will be measured at baseline, post-treatment and at 12-month follow-up.

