### Participants

The study sample will consist of 80 outpatients fulfilling criteria for a diagnosis of Schizophrenia or Schizophrenia Spectrum, Major Depressive Disorder with psychotic symptoms, or Bipolar I Disorder with psychotic symptoms according to DSM-5 criteria, who had never experienced psychotic symptoms prior to the current episode. The diagnosis of all participants will be carried out by physicians with extensive experience in the diagnosis of FEP.

Inclusion criteria are (1) age between 16 and 65 years at the time of first evaluation; (2) have been diagnosed with a first psychotic episode in the last year, with or without pharmacological treatment and/or psychiatric hospitalization; (3) presence of one or more traumatic events causing trauma related symptoms (Impact of Event Scale-Revised, IES-R >0 and Subjective Units of Distress, SUD >5); 4) ability to read and write in Spanish.

Exclusion criteria are: (1) acute suicidality; (2) presence of organic brain diseases; (3) previous trauma-focused therapy in the past 2 years.

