### Statistical Analysis

The distribution of socio-demographic, clinical (including psychological trauma), functionality, quality of life and treatment adherence characteristics among baseline groups will be analyzed using descriptive statistics. Continuous variables with a normal distribution will be analyzed with the Multivariate Variance Analysis. The change of the clinical variables of functionality and quality of life with respect to the baseline assessment at strategic points of the intervention will be analyzed by ANOVA with repeated measurements, including time factors, treatment conditions and their interaction. For those cases in which the premises of normality are not fulfilled, the Wilcoxon test will be used. The differences between groups, for the categorical and main clinical variables, will be analyzed by means of the Chi-square test. Those variables that are statistically significant can be used as covariates for a logistic or linear regression study of the factors associated to the magnitude of the effect and determine which variables are the best predictors of functioning. The effect size index (Hedges g or r de Pearson index) will be estimated in case of correlation indexes of each of the analyses performed. The statistical software used for the analyses will be the latest available version of the SPSS (v. 23).

For the main statistical analysis, we will conduct an intention-to-treat (ITT) analysis. We will impute lost to follow-up with the Last Observation Carried Forward (LOCF) method.

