## Materials and Equipment

### Instruments and Measures

Trauma-related symptoms will be evaluated using the instruments listed in **Table 2**:

Childhood Trauma Questionnaire (CTQ): The CTQ (36), Spanish validation (37), is a self-administered 28-item scale to measure abuse and neglect suffered in childhood on five subscales: emotional, physical or sexual abuse, and emotional or physical neglect, each subscale scored on a 5-point Likert scale. The score for each subscale classifies the severity of the abuse and neglect as: “none to minimal,” “low to moderate,” “moderate to severe” and “severe to extreme”.Global Assessment of Posttraumatic Stress Questionnaire (EGEP-5): The EGEP-5 (38) is a 55-item clinician-applied scale to determine PTSD diagnosis, based on the current DSM-V criteria. This scale consists of three sections: events, symptoms and functioning.The Holmes-Rahe Life Stress Inventory (39); Spanish validation (40) is used to determine which common stressful life events a patient has experienced in the last 12 months, with each life event scored according to a standardized measure of their impact (41) and a total score provided by summing all those applicable to the patient. Although individual characteristics and coping skills should be taken into account when interpreting scores, scores below 150 reflect low levels of stress, scores between 150 and 299 represent a 50% risk of a stress-related illness in the near future and scores above 300 represent an 80% risk (39).Impact of Event Scale - Revised (IES-R): The IES-R (42), Spanish validation (43), is a 22-item self-report measure used to determine the level of subjective distress the subject has experienced over the past week related to a specific stressful life event, with items corresponding directly to 14 of the 17 DSM-IV symptoms of PTSD. Each item is scored on a 5-point Likert scale from 0 to 4, yielding a total score ranging from 0 to 88, with subscale scores for Intrusion, Avoidance and Hyperarousal. Higher scores represent greater subjective distress.Dissociative Experiences Scale (DES): The DES (36), Spanish validation (44), is a 28-item self-report scale which measures the frequency with which an individual experiences a range of dissociative experiences, from normal to pathological. An overall mean score ranges from 0 to 100, and there are subscales for amnesia, dissociation and depersonalization. A total score of over 30 indicate high levels of dissociation.Dissociative Experiences Questionnaire (SDQ-20): The SDQ-20 (45), Spanish validation (46), is a 20-item self-report scale used to measure somatoform dissociation. Each item refers to a physical symptom and is scored from 1 to 5 on a 5-point Likert scale, ranging from “1 = this applies to me not at all” to “5 = this applies to me extremely”, and the patient is then asked if there is a known physical cause. Total scores can range from 20 to 100, with higher scores denoting higher levels of somatoform dissociation.

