
**Table 2 T2:** Measurements to evaluate trauma-related symptoms.

Clinical variable	Measurement interview/self-report	T0 Baseline	T1 Post-treatment 6 months	T2 Post-treatment 12 months
Childhood T.	CTQ	x		
PTSD	EGEP-5	x	x	x
Traumatic events	H-RLSI	x		
Trauma’s impact	IES-R	x	x	x
Dissociation	DES	x	x	x
Somatoform D.	SDQ-20	x	x	x

Childhood T, Childhood trauma; CTQ, Childhood Trauma Questionnaire; PTSD, post-traumatic stress disorder; EGEP-5, Global Assessment of Posttraumatic Stress Questionnaire; H-RLS,: The Holmes-Rahe Life Stress Inventory; IES-R, Impact Event Scale; DES, Scale of Dissociative Experiences; Somatoform D., Somatoform Dissociation; SDQ-20, Dissociative Experiences Questionnaire.

The diagnosis, clinical symptoms and level of functioning are to be assessed using the following instruments (see **Table 3**):

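### If PTSD diagnosis is analysed at T1 and T2, the planned chi-square ignores PTSD status at T0: error rate kept, but power and precision lost (minor)

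*Protocol article*

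**What the plan says.** **Test.** In the protocol article, Statistical Analysis assigns one test to categorical variables: "The differences between groups, for the categorical and main clinical variables, will be analyzed by means of the Chi-square test". No baseline term is attached to it.

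**Other provisions in that section.** The baseline enters through a repeated-measures ANOVA, stated for a different set of variables: "The change of the clinical variables of functionality and quality of life with respect to the baseline assessment at strategic points". A regression is also allowed: "Those variables that are statistically significant can be used as covariates for a logistic or linear regression study". It is optional, chooses covariates by significance, and is aimed at factors related to the size of the effect and at predictors of functioning.

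**Instrument.** Instruments and Measures describes the EGEP-5 as a "55-item clinician-applied scale to determine PTSD diagnosis, based on the current DSM-V criteria".

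**Schedule.** Table 2 has the row "PTSD EGEP-5 x x x", that is, T0, T1 and T2. The abstract agrees: "All variables will be measured at baseline, post-treatment and at 12-month follow-up". Table 1 disagrees: it ticks the EGEP-5 at enrolment only, while the IES-R, DES, SDQ-20 and others carry follow-up ticks.

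**Entry and allocation.** The trauma criterion under Participants is "presence of one or more traumatic events causing trauma related symptoms (Impact of Event Scale-Revised, IES-R >0 and Subjective Units of Distress, SUD >5"), with no PTSD diagnosis required. The biased coin under Randomization Procedure balances group size, age, sex and years of education.

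**The concern.** A PTSD diagnosis at T1 is likely to depend strongly on whether the patient had PTSD at T0. Because entry does not require PTSD, each arm mixes patients who can remit with patients who cannot. Because allocation does not balance PTSD, the arms may also start at different rates.

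A chi-square on T1 or T2 status uses none of this. Two costs follow. The variation explained by T0 status stays in the error term, which lowers power. Any chance T0 difference between arms stays, in large part, in the reported T1 difference. Study Aim says that clinical scales will be used to evaluate changes from baseline, and a comparison of follow-up status alone does not do that. The T0 EGEP-5 needed for adjustment is collected under both Table 1 and Table 2.

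**Working it through.** **Plan's own figure.** There is none for PTSD. The only sample-size calculation is for relapse, at alpha 0.005, with 36 per group needed and about 40 per arm recruited. The check below therefore rests on assumptions.

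**Inputs from the article.** 40 per arm; alpha 0.005 (Computation of Sample Size), with 0.05 as the conventional alternative; 12.4% PTSD prevalence in psychosis (Introduction). The Introduction also gives 40–80% for post-psychotic post-traumatic syndrome in first-episode patients, which is a related condition and not the same as PTSD. The T0 PTSD rate in this sample is therefore unknown and is varied.

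**Assumed inputs, not in the article.** T0 PTSD rate p = 12.4, 30, 50 or 70%; remission by T1 of 25% on TAU and 55% on EMDR; 5% new onset; PTSD allocated 1:1 at random; complete data.

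**Step 1. Expected T1 difference.** T1 rate = p(1 − remission) + (1 − p)(0.05). At p = 0.50, TAU is 0.50 × 0.75 + 0.50 × 0.05 = 0.40 and EMDR is 0.50 × 0.45 + 0.50 × 0.05 = 0.25. In general the difference is 0.30p, so 9, 15 and 21 points at 30, 50 and 70%.

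**Step 2. Carry-over of a T0 difference with no treatment effect.** The T1 risk is 0.75 with PTSD at T0 and 0.05 without, so 0.75 − 0.05 = 0.70 of any T0 difference passes into T1. A 10-point T0 gap shifts the T1 difference by about 7 points.

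**Step 3. How often the arms differ at T0.** The SD of the T0 difference is √(2p(1 − p)/40): 0.102 at 30% and 70%, 0.112 at 50%. By the exact binomial, a gap of more than 10 points (at least 5 patients of 40) occurs in 27% of trials at 30% or 70%, and in 31% at 50%.

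**Step 4. Precision.** At p = 0.50 with no effect, the T1 variance per patient is 0.40 × 0.60 = 0.24. Within T0 strata it averages 0.50 × (0.75 × 0.25) + 0.50 × (0.05 × 0.95) = 0.1175. The standard error of the arm difference is √(2 × 0.24/40) = 0.110 unadjusted, against about √(2 × 0.1175/40) = 0.077 adjusted.

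**Step 5. Power by simulation**, Pearson chi-square against a Mantel-Haenszel test stratified on T0 PTSD:

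| T0 PTSD | alpha 0.05: chi-square | alpha 0.05: stratified | alpha 0.005: chi-square | alpha 0.005: stratified |
|---|---|---|---|---|
| 12.4% | 9% | 9% | 0.6% | 0.8% |
| 30% | 17% | 23% | 2.7% | 5.0% |
| 50% | 29% | 42% | 8.4% | 14.1% |
| 70% | 50% | 60% | 17.9% | 26.5% |

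With no effect, chi-square type I error at nominal 5% is 5.0–5.8%; the stratified test stays at or just below 5%.

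**Step 6. Sensitivity to the assumed rates.** With an odds ratio of 0.25 in both strata and T1 risks under TAU of 0.70 and 0.10, or 0.80 and 0.05 (PTSD at T0 and none), the gain at alpha 0.05 is 4–5 points at 12.4% T0 PTSD, 13–20 at 40%, 12–19 at 60% and 5–11 at 80%. With no effect, in the subset of trials where EMDR starts at least 12.5 points higher, chi-square rejects 11–22% of the time and the stratified test 4–6%.

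**The case against.** **The endpoint is inferred.** This stands. Study Aim and Hypotheses name post-traumatic stress and trauma-related symptoms, not PTSD diagnosis or remission, and Statistical Analysis names neither PTSD nor the EGEP-5. The EGEP-5 also has symptom and functioning sections, so it might be analysed as a score. A reader might take PTSD diagnosis for the trial's clearest trauma endpoint; the article gives it no such rank.

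**The schedule is contradicted.** This stands. If Table 1 governs, there is no T1 or T2 diagnosis to test and the point is empty.

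**The test is valid.** This stands too. A reader might infer that the chi-square is biased or produces too many false positives. It does not: over all randomizations its error rate is about 5%. The 7-point shift and the 11–22% rejection rate are conditional on an unlucky allocation, which the nominal alpha already covers.

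**A regression is already allowed.** This is correct, so the chi-square is not the only provision that could touch a categorical variable. But the regression is optional, significance-driven and directed elsewhere, so it does not fix an adjustment for T0 PTSD.

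**Covariates for secondary outcomes are often left to a fuller document.** This is fair in general. Here, however, the article does name a test for categorical variables, and that test is less efficient than one using data already collected.

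**The gain is modest.** At alpha 0.005 both tests have low power, and expected losses of 10–15% would lower it further. This limits the importance of the point but gives no reason to prefer the unadjusted test.

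**Conclusion.** The point holds, at minor severity and on two conditions: that the T1 and T2 EGEP-5 assessments stand, and that they are analysed as a diagnosis. The chi-square would then keep its nominal type I error but lose power and precision, and leave about 0.70 of any chance T0 difference in the T1 result when there is no effect.

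Under the assumed rates and two-sided alpha 0.05, the power given up is about 6, 13 and 10 points at T0 PTSD rates of 30, 50 and 70%. At the article's 0.005 it is about 2, 6 and 9 points. At 12.4% there is no gain under these rates, and 4–5 points at alpha 0.05 under the alternative set. All of these sizes rest on remission, onset and T0 rates that the article does not give. The direction depends only on T0 status predicting later status. The relapse outcome and the continuous scales are not affected.

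**What to change.** 1. Reconcile Table 1 with Table 2 and the abstract on whether the EGEP-5 is given at T1 and T2, and state whether it is analysed as a diagnosis.
2. If so, add one sentence to Statistical Analysis: PTSD diagnosis at T1 and at T2 will be compared between arms by a Mantel-Haenszel test stratified on T0 PTSD status, or by logistic regression with T0 PTSD status as a prespecified covariate, in place of the plain chi-square. Report the adjusted difference with its 95% CI.
3. Remission among patients with PTSD at T0 may be added as a supplementary description.

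The cost is a table correction and one sentence of analysis wording. T0 EGEP-5 is already collected, so the change of test adds no patient procedure and leaves the sample size as it is.

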### Randomization Procedure

After the baseline (T0) assessment (see later), we will randomly allocate participants to the EMDR or TAU group following a biased coin procedure (29). We want to note that in small clinical trials, simple randomization may lead to substantial imbalance in the relevant confounding factors between groups. The biased coin procedure attempts to balance these confounding factors but it still randomizes the patients and conceals their allocation (30). It has been included in the international guidelines for drug clinical trials (31) adopted by the European Community, Japan, United States FDA, Canada and Switzerland (32).

Specifically, a computer in a central location will allocate the patients as follows: (a) it will randomly allocate the first two patients to one group or the other with p = 0.5, (b) it will allocate the next patients as follows: (b1) if one group already includes at least two more patients than the other group, it will randomly allocate the patient allocated to the smallest group with p = 0.8, (b2) otherwise, it will first simulate that the patient is allocated to EMDR and calculate the sum of the between-group square standardized differences in age, sex and years of education, it will then simulate that the patient is allocated to TAU and recalculate the sum, and finally it will randomly allocate the patient to the group associated to the smallest sum with p = 0.8. Following this procedure, the final groups should be balanced in size and matched in age, sex and years of education. An independent researcher in a central location will control the computer program that will carry all steps of the randomization process.

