### Computation of Sample Size

The study aims to assess the relative efficacy of an EMDR intervention protocol for patients with FEP versus TAU mainly in terms of stabilization and clinical improvement, reduction of anxious, depressive, somatic and/or psychotic symptoms, among others. For this reason, the main variable used is the number of clinical relapses after the intervention, with a follow-up of up to 12 months. Using previous studies as a basis (33), the sample size has been calculated based on a survival analysis with the statistical package “powerSurvEpi” for R, (http://www.r-project.org/) using an alpha = 0.005 instead of 0.05 to allow correction for multiple comparisons. The number of patients required to detect a hazard ratio = 2 in a Cox regression with a statistical power of 80% and alpha = 0.005 is n = 36 per intervention group (two groups, total n = 72). According to Chambless and Hollon (29), a sample of this size should show clinically relevant differences. Assuming a loss percentage of approximately 10–15% of the patients in the study, it would be necessary to recruit approximately 80 patients, 40 for each branch of intervention.

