
## Limitations

One limitation of this study is the inclusion of both affective and non-affective FEP, as well as comorbid substance use disorders, leading to a more heterogeneous sample. These inclusion criteria were decided on to ensure the study was carried out on a representative real-world population. We suggest this limitation can be addressed by matching the samples in both arms. Additionally, the main underlying clinical variable common to all patients is the presence of comorbid psychological trauma. Another potential source of bias is the lack of control regarding pharmacological treatment. To partly overcome this limitation, a ‘pharmacological treatment’ variable will be included and, to the extent it is possible, patients in the study should not have their drug therapy altered once they are stabilized. As our unit has extensive experience in treating FEP patients and uses standardized treatment protocols, this will also help limit this as a potential source of bias.

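### Age, sex and years of education steer the allocation but are in none of the stated between-group tests; the cost is possible lost power, not bias or false positives

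*Protocol article*

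**What the plan says.** **Allocation.** Under Randomization Procedure, a computer will simulate each patient's placement in either arm and "calculate the sum of the between-group square standardized differences in age, sex and years of education". It then favours the arm with the smaller sum, with probability 0.8. A size rule takes precedence when the arms differ by two or more. The expected result is that "the final groups should be balanced in size and matched in age, sex and years of education".

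**Between-group tests.** Under Statistical Analysis, change in functioning and quality of life is analysed by "ANOVA with repeated measurements, including time factors, treatment conditions and their interaction", with a Wilcoxon test where normality fails. For other variables: "The differences between groups, for the categorical and main clinical variables, will be analyzed by means of the Chi-square test". None of these contains age, sex or education.

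**Covariates.** The same section says: "Those variables that are statistically significant can be used as covariates for a logistic or linear regression". The sentence goes on to give the purpose of that regression, a "study of the factors associated to the magnitude of the effect and determine which variables are the best predictors of functioning". It does not say which test decides significance.

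**Medication.** To address uncontrolled drug treatment, Limitations says that a pharmacological treatment "variable will be included and, to the extent it is possible", drug therapy is to stay unchanged after stabilisation. Neither the time of measurement nor the model is given.

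**The concern.** Forcing balance on a prognostic factor removes part of the chance variation between arms. A test that ignores the factor still counts that variation in its standard error. The standard error is then too large, the true type I error falls below nominal, and some of the precision bought by the allocation is wasted. In a trial of 80 patients that can matter.

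Selecting covariates by p value does not repair this. The model then depends on the data. If selection were by between-group difference, it would pass over exactly the factors that the allocation has balanced.

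The medication variable raises a related, conditional question. If it were measured after randomisation and put into a treatment-effect model, it would condition on something that treatment may have influenced.

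**Working it through.** The plan gives no figure on this point, so there is none to reproduce.

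**Inputs from the article.** N = 80, 40 per arm; allocation probability 0.8; size rule at a difference of two; balancing on age, sex and education (Randomization Procedure, Computation of Sample Size).

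**Assumed inputs, not in the article.** Joint share of outcome variance explained by the three factors (R²) from 0 to 0.5, split equally; standardised treatment difference 0.63; for a binary outcome, a log odds ratio per SD of each factor from 0 to 0.69 and a treatment log odds ratio of −1.3. Sex is 50/50 and there is no dropout.

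**Step 1: how much balance the rule produces.** In 4,000 simulated trials the SD of the between-arm difference per factor, in SD units, was 0.082 (age), 0.073 (sex) and 0.082 (education). Simple randomisation gives 2/√80 = 0.224. No balancing factor differed between arms at p < 0.05 in any trial.

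**Step 2: type I error by formula.** For outcome variance 1, the unadjusted test assumes that the mean difference has variance 4/80 = 0.05. The mean squared SD from step 1 is (0.0824² + 0.0729² + 0.0819²)/3 = 0.00627. The actual variance is therefore about (1 − R²) × 0.05 + R² × 0.00627, and the true size is 2 × [1 − Φ(1.96/√ratio)], with ratio = actual variance/0.05.

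| R² | Actual variance | Ratio | Size by formula | Simulated, unadjusted | Simulated, adjusted |
|---|---|---|---|---|---|
| 0 | 0.0500 | 1.000 | 5.0% | 5.1% | 4.8% |
| 0.1 | 0.0456 | 0.913 | 4.0% | 4.1% | 5.1% |
| 0.2 | 0.0413 | 0.825 | 3.1% | 3.2% | 5.8% |
| 0.3 | 0.0369 | 0.738 | 2.2% | 2.2% | 5.3% |

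The Monte Carlo standard error is about 0.35 points. A repeat simulation gave somewhat milder sizes, about 4% and 3% at R² 0.2 and 0.3. The direction is the same.

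**Step 3: power, continuous outcome at one time point, two-sided alpha 0.05.**

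| R² | Unadjusted | Adjusted | Gain (points) |
|---|---|---|---|
| 0 | 79.7% | 79.4% | −0.3 |
| 0.1 | 79.3% | 81.9% | 2.6 |
| 0.2 | 82.4% | 87.3% | 4.9 |
| 0.3 | 83.2% | 91.5% | 8.3 |

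At a difference of 0.6, one repeat gave gains of about 4 to 7 points at R² 0.2 to 0.3. A smaller run (800 trials) gave 78% against 84% and 80% against 89%.

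Computation of Sample Size plans "using an alpha = 0.005 instead of 0.05 to allow correction for multiple comparisons". At that level (taken as two-sided) the figures are 46% against 52%, 47% against 60% and 47% against 68% at R² 0.1, 0.2 and 0.3. The article states this alpha for sizing the relapse comparison and does not say that it governs the scales.

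**Step 4: binary outcome, chi-square against adjusted logistic regression, alpha 0.05.**

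| Log odds ratio per SD | Chi-square size | Chi-square power | Adjusted power |
|---|---|---|---|
| 0 | 5.7% | 74.7% | 74.9% |
| 0.23 | 5.1% | 71.1% | 72.1% |
| 0.46 | 4.2% | 65.6% | 69.7% |
| 0.69 | 3.7% | 57.6% | 67.0% |

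The adjusted logistic test has size 5.3 to 5.7% throughout. The Cox model was not simulated.

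**Step 5: the planned time-by-treatment test.** If the factors' effects are constant over time, they cancel in the change from baseline. With such effects, 3,000 simulated null trials gave an unadjusted interaction test of size 4.3%, 4.7% and 5.1% at R² 0.1, 0.2 and 0.3. The single-time test in the same trials gave 3.8%, 3.3% and 2.1%.

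**The case against.** The strongest reply is that the p-value sentence is not the covariate rule for the treatment comparison. Read to its end, it describes an optional regression on effect magnitude and predictors of functioning. This stands. A reader might infer that the plan uses significance testing in place of adjustment in its main comparison; the article does not say so. The fault in the treatment comparisons is that the listed tests are unadjusted.

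A reader might also infer that covariates enter only after a significant between-group difference, so that the balanced factors could never be chosen. The selecting test is not stated. If it is association with outcome, the factors could be chosen, although the choice would still be data-driven. Nor does the section clearly plan baseline significance tests; it describes baseline groups with descriptive statistics.

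Third, the repeated-measures interaction test is largely unaffected, as step 5 shows. This stands so long as the factors do not predict change, on which the article is silent.

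Fourth, covariate lists are commonly left to an analysis plan that is not shown. This has weight, but the article does name its tests and the terms of its ANOVA, and the p-value wording is stated. Both can be judged as written.

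Last, the medication point is conditional. One might infer that the variable is measured after randomisation and would remove part of the treatment effect. Limitations gives neither time nor model. It also concerns drug therapy, whereas hypothesis 4 concerns adherence.

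**Conclusion.** The point holds in limited form. The allocation uses three factors that no stated between-group test includes, and the only covariate wording selects by significance. If the factors are prognostic, unadjusted single-time and chi-square comparisons are conservative and lose power. "Mis-sized" should not be read as an excess of false positives or a biased estimate; the calculations show neither.

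For a continuous outcome at alpha 0.05 the loss is nil at R² = 0, about 3 points at 0.1, and about 4 to 8 points at 0.2 to 0.3, with one small run nearer 10 at 0.3. For a binary outcome it runs from nil to about 9 points at the strongest setting tried. All of this rests on assumed prognostic strength. The interaction test suffers only as far as the factors predict change, and the loss in a Cox analysis of relapse has not been quantified. This is a worthwhile and cheap improvement rather than a threat to validity.

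**What to change.** - State that age, sex and years of education enter the relapse model (Cox or logistic) and the scale models, whatever their significance.
- For scales, add the baseline score as a covariate. In simulation this gave a larger power gain than the three factors; its size depends on the correlation between baseline and follow-up, which the article does not give.
- Drop p-value-based covariate selection from every model that estimates a treatment effect. If it is kept at all, confine it to the regression on predictors of functioning and effect magnitude, labelled exploratory.
- If the pharmacological treatment variable enters a treatment-effect model, use its baseline value only and report later medication changes by arm.

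**Cost.** Wording, and about three to four degrees of freedom. Age, sex and education are already needed for allocation. If the factors prove unrelated to outcome, the simulated power cost was under one point (79.7% against 79.4%). Adjusted odds or hazard ratios are conditional on the covariates and should be reported as such.

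### If the effect in question is EMDR versus TAU, regressing outcome on covariates tests prognosis and does not show what the size of that effect depends on

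*Protocol article*

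**What the plan says.** One sentence in the protocol article, Methods, Statistical Analysis, carries this point. It selects candidates by significance ("Those variables that are statistically significant"), gives them a role ("can be used as covariates for a logistic or linear regression study of the factors associated to the magnitude of the effect"), and adds a second aim ("determine which variables are the best predictors of functioning"). The sentence just before it describes chi-square comparisons between groups.

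The only interaction named in the section belongs to a different analysis, the "ANOVA with repeated measurements, including time factors, treatment conditions and their interaction". That term is time by treatment. No term combining a baseline factor with treatment is named for the regression.

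The section does not define the magnitude of the effect. It gives no model equation and does not say whether arm is in the regression.

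**The concern.** The sentence joins two questions that need different model terms. Asking which factors go with a larger or smaller treatment effect is a question about effect modification: does the EMDR-minus-TAU difference change with the factor? Asking which variables best predict functioning is a question about prognosis. A variable entered as a covariate answers the second and not the first.

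Two errors are at stake. A variable such as baseline PANSS or GAF, if it predicts outcome in both arms, could be presented as something on which the benefit of EMDR depends even though the benefit is the same for everyone. Conversely, a factor that does separate patients who benefit from those who do not would usually show no signal.

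The Limitations section acknowledges a clinically mixed sample (affective and non-affective psychosis, comorbid substance use), so readers will look for a statement about who benefits.

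**Working it through.** **Inputs.** The article gives no figure for this regression, so there is nothing to reproduce. From Computation of Sample Size come 72 patients required and about 80 recruited (72/0.90 = 80 at 10% loss). All slopes and interaction sizes below are assumptions, shown as ranges. Tests are two-sided at 5%.

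**What each coefficient measures.** Let A = +½ for EMDR and −½ for TAU, z a standardized baseline factor, and

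Y = α + τA + βz + δAz + error.

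- EMDR minus TAU at a given z is τ + δz. The factor bears on the size of the effect only if δ ≠ 0.
- The slope on z is β + δ/2 under EMDR and β − δ/2 under TAU. With 1:1 arms, the coefficient of z in a model with A and z alone estimates their average, β.

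The first aim is therefore about δ, while a covariate test is about β. Neither determines the other.

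**Precision (residual SD 1).** SE(β) ≈ 1/√n and SE(δ) ≈ 2/√n. At n = 80 these are 0.112 and 0.224.

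**Simulation 1** (8,000 trials per setting, arm effect 0.5 SD, residual SD 1). Share of trials with a significant result:

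| Assumed truth | Covariate, n = 72 | Arm-by-factor, n = 72 | Covariate, n = 80 | Arm-by-factor, n = 80 |
|---|---|---|---|---|
| β = 0, δ = 0 | 4.9% | 4.4% | 4.9% | 5.4% |
| β = 0.3, δ = 0 | 68% | 4.7% | 75% | 5.1% |
| β = 0.5, δ = 0 | 98% | 4.9% | 99% | 4.7% |
| β = 0, δ = 0.5 | 5.8% | 53% | 5.7% | 56% |
| β = 0, δ = 0.7 | 6.3% | 80% | 5.8% | 85% |
| β = 0, δ = 1.0 | 7.2% | 97% | 7.0% | 99% |

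Check by formula at n = 80, β = 0.3: 0.3/0.112 = 2.68, and Φ(2.68 − 1.96) ≈ 0.77, against 75% simulated.

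**Simulation 2** (4,000 trials per setting, n = 80, arm effect 0.5 SD, residual variance 1 − ρ²). With δ = 0 and correlation ρ = 0.2, 0.3, 0.4 and 0.5, the covariate test is significant in 43%, 77%, 96% and 99.8% of trials; the interaction test rejects in 4.4% to 5.5%. With ρ = 0 and δ = 0.6 or 0.8, the covariate test is significant in about 6%, against 74% and 92% for the interaction test.

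**How much the interaction test can deliver.** The larger values of δ are generous. With an average effect of 0.5 SD and δ = 0.8, the effect is 0.5 − 0.8 = −0.3 SD at one SD below the mean of the factor and 0.5 + 0.8 = 1.3 SD at one SD above, a reversal of sign. For smaller modifications at n = 80:

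- δ = 0.2: 0.2/0.224 = 0.89; power ≈ Φ(0.89 − 1.96) + Φ(−0.89 − 1.96) ≈ 0.15.
- δ = 0.3: 0.3/0.224 = 1.34; power ≈ Φ(1.34 − 1.96) ≈ 0.27.

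The half-width of a 95% CI for δ is about 1.96 × 0.224 = 0.44 SD per SD.

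**The case against.** A reader might infer that the plan enters these variables only as covariates and so rules out interactions. The text does not say that. Its wording is permissive and excludes no term, and a condensed article may leave the exact terms of an optional regression to a fuller document. This stands, so the absence of an interaction term is not itself the point. What remains is that the role the article does state does not serve the first aim it states.

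A reader might also infer that ordinary predictors will be reported as modifiers of the EMDR effect. The article never calls these variables modifiers or moderators, and none of its objectives or hypotheses asks who benefits more. Misreporting is a risk of the wording and not something the plan commits to.

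The magnitude of the effect could mean size of change, since the section also speaks of change from baseline. That reading is possible, which is why the point is conditional. The treatment difference is the more natural reading: Computation of Sample Size frames the study as relative efficacy against TAU, and the next analysis sentence but one-step topic, effect size indices, follows directly. If size of change was meant, a covariate pooled over arms is still prognostic and should be described so.

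Finally, the simulations illustrate a known property under assumed parameters and cover linear regression only. They also omit the plan's significance screen, so the percentages are not error rates of the plan as it would be run. This stands too. The distinction between β and δ does not depend on those choices, and a screen based on differences between groups does not select for effect modification.

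**Conclusion.** The point holds conditionally. If the effect means EMDR versus TAU, the covariate role stated in the article answers a prognostic question, and the sentence merges that question with the one about the size of the effect. For the second aim, predictors of functioning, covariates are the right tool.

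Under the assumed slopes, a purely prognostic factor would be significant far more often than 5%, and a pure modifier hardly more often than 5%. The exact percentages rest on assumed parameters, a linear model and unscreened factors. The direction does not.

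Severity is minor. The regression is optional and secondary, and it does not touch the primary relapse comparison.

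**What to change.** Split the sentence into two analyses.

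1. **Factors related to the size of the EMDR effect.** Choose in advance a short list of baseline factors already collected (for example affective versus non-affective diagnosis, IES-R, CTQ), not screened by significance. For each, fit arm, factor and arm-by-factor. Read effect modification only from the interaction estimate with its 95% CI, and label the analysis exploratory.
2. **Predictors of functioning.** Keep the main-effect regression, with arm in the model, and describe its results as prognostic only.

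If effect modification is not intended, remove the reference to the magnitude of the effect and call the whole analysis prognostic.

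The cost is a few sentences, one extra model term and no new data. The downside is imprecision: with about 80 patients, power is high only for assumed modifications of roughly 0.6 to 0.8 SD per SD or more, so a non-significant interaction must not be read as evidence that the effect is uniform.
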